### Calculation of sample size

The sample size of this study was calculated on the basis of the primary outcome of the leprosy chemoprophylaxis among contacts using rifampicin associated with BCG vaccine. For the occurrence of this outcome a minimum follow-up time was set at 1 year.

Sample size calculations were based on the proportion of contacts that would likely develop leprosy per intervention group, currently estimated at 5% for the placebo group and 2% for the rifampicin group. With an allocation ratio of 2:1, the difference of 3 percentage points, a statistical power of 80%, and a significance level of 5%, (corrected to 0.025 to account for the interim analysis), the study requires 829 participants in the intervention group and 415 controls for a total 1244 participants. Estimating a 20% loss during follow-up (based on previous ASA data), the total sample size would total 1493 participants (995 in the treatment group and 498 controls). This sample size is appropriate for the analysis of time to failure enabling the study to detect more subtle effects (hazard ratio 0.67). Assuming a 30% seropositivity for PGL-1 among controls, this sample size will provide 85% power to detect an 8 percentage point difference from the treatment group. For 2.5% LID-positive controls, the study has 77% power to detect a 2 percentage point difference. For 35% IFN-γ-based susceptibility the study has an 80% power to detect an 8 percentage point difference. The calculations were performed via PASS11 software [23].

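### The claim that this sample size can detect a hazard ratio of 0.67 is not supported by the plan's own inputs

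*Protocol article*

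**What the plan says.** All of the figures are in the section Calculation of sample size of the protocol article. The leprosy risks are "currently estimated at 5% for the placebo group and 2% for the rifampicin group". Allocation is 2:1 and power is 80%, with "a significance level of 5%, (corrected to 0.025 to account for the interim analysis"); whether the test is one- or two-sided is not stated. The result is that "the study requires 829 participants in the intervention group and 415 controls for a total 1244 participants". After an allowance for 20% loss, "the total sample size would total 1493 participants (995 in the treatment group and 498 controls"). The next sentence extends this number to the time-to-event analysis: "This sample size is appropriate for the analysis of time to failure enabling the study to detect more subtle effects (hazard ratio 0.67"). No power, event count, event rate or time horizon accompanies that figure.

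The same section sets a minimum of 1 year of follow-up. The Follow-up and Trial status sections add recruitment from July 2015 to July 2020, fixed visits to month 12, and then case finding through self-referral and the national leprosy database until July 2021. No incidence beyond the 5% is given. The Statistical analysis section names Cox regression and the log-rank test.

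**The concern.** The power of a log-rank or Cox analysis depends on the number of events. When events are rare, analysing time to disease in the same people adds almost nothing to a comparison of proportions. A design that has just been given 80% power for an HR near 0.39 should not also be sensitive to 0.67 unless many more events are expected than the 5% implies, and the article does not say that they are.

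What is at stake is how a null result is read. Someone relying on the sentence would take a non-significant result as evidence against a one-third reduction in hazard. If 5% is the whole placebo risk, the trial would miss such an effect at least seven times in ten.

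**Working it through.** **Inputs from the article.** Placebo risk 0.05, rifampicin risk 0.02, allocation 2:1, 829 + 415 = 1244 evaluable, 995 + 498 = 1493 enrolled, claimed HR 0.67.

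**Step 1: reproduce the stated sample size.** Use the pooled two-proportion formula without continuity correction. The pooled risk is (0.05 + 2 × 0.02)/3 = 0.03.

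Controls = [1.96 × √(1.5 × 0.03 × 0.97) + 0.842 × √(0.05 × 0.95 + 0.02 × 0.98/2)]² / 0.03² ≈ 415.

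This matches the stated 415 controls, and twice that is 830 against the stated 829. The level that reproduces the plan is therefore two-sided 5% (one-sided 0.025). Two-sided 0.025 would need 499 controls, 1497 in all. The implied HR is ln 0.98 / ln 0.95 = 0.39.

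**Step 2: events needed for HR 0.67 (Schoenfeld, 80% power).**

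- Two-sided 5%: (1.96 + 0.842)² / [(2/9) × (ln 0.67)²] = 7.85 / 0.0356 ≈ 220.
- Two-sided 0.025: 267.

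**Step 3: events expected if 5% is the cumulative placebo risk.** The rifampicin risk under HR 0.67 is 1 − 0.95^0.67 = 0.0338.

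- 1244: 415 × 0.05 + 829 × 0.0338 = 48.8.
- 1493, no loss: 498 × 0.05 + 995 × 0.0338 = 58.5.

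**Step 4: power** = Φ(√(events × 2/9) × |ln 0.67| − z), with |ln 0.67| = 0.400.

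- 1244: Φ(1.318 − 1.960) = 26%.
- 1493: Φ(1.444 − 1.960) = 30%.
- With z = 2.241 (two-sided 0.025): 18% and 21%.

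The HR at which power reaches 80%, with events recomputed for each HR, is 0.374 (1244) and 0.416 (1493) at two-sided 5%. Other methods at the same level agree: power is 29–33% with the Freedman form and 30–34% with a two-proportion test. A one-sided 5% test gives 37–42%. Reaching 80% at two-sided 5% would take a cumulative placebo risk of about 22% (1244) or 19% (1493).

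**Step 5: longer follow-up.** Assumption, not in the article: 5% is an annual risk with constant hazard λ = −ln 0.95 = 0.0513. Recruitment is even over five years, so follow-up is uniform from 1 to 6 years.

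- Mean placebo risk: 1 − (e^(−λ) − e^(−6λ))/(5λ) = 16.2%. With 0.67λ in place of λ, the rifampicin risk is 11.2%.
- Events: 415 × 0.162 + 829 × 0.112 ≈ 160, and 498 × 0.162 + 995 × 0.112 ≈ 192.

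| Assumption on the 5% | N | Events under HR 0.67 | Power, two-sided 5% | Power, two-sided 0.025 | Detectable HR, 80% power, two-sided 5% |
|---|---|---|---|---|---|
| Cumulative | 1244 | 49 | 26% | 18% | 0.37 |
| Cumulative | 1493, no loss | 59 | 30% | 21% | 0.42 |
| Per year, constant, even accrual | 1244 | 160 | 67% | 56% | 0.62 |
| Per year, constant, even accrual | 1493, no loss | 192 | about 75% (74.5%) | 65% | 0.65 |

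**The case against.** The strongest defence is that the HR 0.67 sentence concerns the time-to-event analysis, which uses follow-up beyond the first year. The article ties the 5% only to a minimum of 1 year and never calls it the risk at study end. This stands. A reader might infer that power for HR 0.67 simply is 26–30%, but that holds only if no events accrue beyond the 5%.

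A reader might also infer that no amount of follow-up could help. The document does not support so flat a statement. If 5% per year persists, three scenarios reach or approach 80%:

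- A one-sided 5% test with even accrual and all 1493 retained gives 83.5%. That is not the level that reproduces the stated sample size, and it ignores the planned 20% loss.
- If all 1493 were enrolled by the end of year 3, with 3–6 years of follow-up and no loss, there would be about 244 events and 84% power at two-sided 5% (77% with 1244). The article allows recruitment to stop at the interim analysis but does not state this scenario.
- Six years of follow-up for all 1244 gives 264 events, with power of 87% at two-sided 5% and 79.6% at two-sided 0.025. Recruitment to July 2020 with final analysis in July 2021 rules this out.

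Nor can a sustained hazard be dismissed as contradicting the rationale. The Background reports an excess of cases soon after vaccination, not that cases then stop, and the Follow-up section itself appeals to the slow course of the disease.

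The article also promises 95% confidence intervals, which limits misreading of a null result.

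**Conclusion.** The concern holds in this form: the HR 0.67 statement has no support in the inputs given. On the only leprosy risk in the article, read as cumulative, the trial has 49–59 of the roughly 220 events needed, 26–30% power and a detectable HR of about 0.37–0.42. On the generous assumption of a constant 5% per year with even accrual, power is about 67–75% and the detectable HR about 0.62–0.65, still short of the claim. These figures rest on the Schoenfeld approximation, two-sided 5%, proportional hazards and, for the upper end of each range, no loss among 1493.

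A reader might infer that the interim judgement on lack of effectiveness rests on the same figure. The document does not support that. The Statistical analysis section refers the interim decision to the effect the trial was designed to find, to accumulated events and to the trend between groups, and it never mentions HR 0.67. The stated sample size, the 5% against 2% comparison and the choice of tests do not depend on it either. The error lies in the stated sensitivity of the time-to-event analysis.

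**What to change.** Withdraw the HR 0.67 claim, or replace it with a detectable HR stated together with its power, event count, alpha and sidedness, assumed placebo risk and follow-up horizon. On the present inputs, at 80% power and two-sided 5%, that is about 0.37–0.42 if 5% is the cumulative placebo risk. It is about 0.62–0.65 only if 5% per year is assumed to persist under the planned recruitment calendar. State also that HR 0.67 needs about 220 events (267 at two-sided 0.025). If the sponsor holds a longer-term incidence that would supply them, give that rate.

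The cost is a sentence or two. Nothing in the design changes, but the stated sensitivity becomes less favourable.

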### Inclusion and exclusion criteria

The eligibility criteria are sufficiently broad to encompass most potential beneficiaries and yet protect the study from any selective or informational bias. The inclusion criteria are: 1) contacts of MB leprosy patients who agree to undergo chemoprophylaxis; 2) ages 6 months to 70 years; 3) an expressed willingness to undergo both clinical and anti-PGL-1 evaluations; 4) availability for follow-up; and 5) a firm commitment to return for vaccination within 2 months and be clinically evaluated at the end of 12 months. The minimum period for detecting the postulated effect will be 12 months.

Exclusion criteria are: 1) clinical or laboratory confirmation of leprosy at baseline; 2) BCG vaccination within the preceding 12 months (to prevent vaccine-related changes in the immune response), except for infants between 6 and 12 months of age (leprosy detection in infants indicates active transmission and the possibility of having other MB cases in the contact cluster); 3) contacts with immunosuppression and/or a history of tuberculosis in any of its forms; 4) pregnancy at any stage or refusal to undergo a urine pregnancy test; and 5) refusal to sign the informed consent form (ICF).

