After signing the forms, 16 ml of blood is collected from adults and contacts aged 12 to 17 years for the baseline identification of the following immunological markers: anti-PGL-1, anti-LID-1, and IFN-γ during the first evaluation, at the end of the second month (prior to BCG immunization), and 12 months subsequent to the initial intervention. All participants will undergo digital pulp blood sampling for rapid anti-PGL-1 testing during the initial evaluation and after 12 months following intervention. Children under 12 years of age will have only a digital pulp blood sample collected for rapid anti-PGL-1 test. This test has been validated by Bührer-Sékula et al. [10], and a simple verification of the agreement with the results of the enzyme-linked immunosorbent assay (ELISA) (anti-PGL-I) in adults will be conducted in this study to inform of the limitations of the results in children, for whom ELISA (anti-PGL-I) will not be available.

Lymph from the right earlobe is obtained by dermal scraping for DNA/ML molecular investigation (PCR) during the first evaluation, but only from the participants over 12 years of age, since children under 12 years of age are less able to bear the discomfort. Another lymph sample is collected at the end of the second month in the event the result of the first examination is either positive or inconclusive. Lymph collection follows MH guidelines, according to which the specimen is stored in a sterile bottle immersed in a 70% alcohol solution [19].

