### Analyses of outcomes based on immunological and molecular parameters

The quantitative variables analyzed will be those related to the ELISA results on anti-PGL1, LID-1, and IFN-γ. The optical density (OD) of each will be read at 450 nm. PGL-1 samples with OD > 0.25 will be considered positive while LID-1 samples will be considered positive with OD > 0.3. As for IFN-γ, the reading will be performed according to the manufacturer’s recommendations (eBioscience®, San Diego, CA, USA).

Frequency distribution will be constructed to detect asymmetries and the need for scale transformation. The primary analysis will address measures of the central tendencies (mean and median), and those of dispersion (i.e., interquartile range, variance, and standard deviation).

For the continuous variables, paired measurements for each individual will result from blood samples obtained before receiving rifampicin and during the contact visit 2 months after receiving rifampicin and before receiving the BCG vaccine. The results obtained 12 months after the first blood collection will also be submitted to paired analysis with the *t* test comparing the mean values of any changes between the two groups.

The main explanatory variable is intervention (rifampicin/placebo). Bivariate and multivariate analyses (linear regression model) will consider the following major covariates: age group, bacilloscopic index (BI), and type of coexistence with the index case. The response variables will include the anti-LID-1, anti-PGL-1, and IFN-γ measurements on a continuous scale. The effect of the intervention will be evaluated and adjusted for the effects of the other explanatory variables.

Regarding the PCR results (positive/negative), bivariate and multiple analyses (logistic regression model) will include the same previously mentioned explanatory variables: age group, BI, and type of cohabitation with the index case. A 5% significance level will be adopted, and 95% confidence intervals will be constructed for the estimates. Data management will use Microsoft Access®, and statistical analyses will be conducted using SPSS version 22.0 (IBM Corp., 2013).

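### The stated marker power (PGL-1 85%, LID-1 77%, IFN-γ 80%) makes no deduction for contacts under 12, who give no venous blood

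*Protocol article*

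**What the plan says.** All statements are in the Methods of the protocol article.

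- **Calculation of sample size.** Before loss, "the study requires 829 participants in the intervention group and 415 controls for a total 1244 participants". After allowing 20% for loss during follow-up, "the total sample size would total 1493 participants (995 in the treatment group and 498 controls"). Three marker statements follow: "Assuming a 30% seropositivity for PGL-1 among controls, this sample size will provide 85% power to detect an 8 percentage point difference"; "For 2.5% LID-positive controls, the study has 77% power to detect a 2 percentage point difference"; and "For 35% IFN-γ-based susceptibility the study has an 80% power to detect an 8 percentage point difference". None mentions participants without a sample, a visit, a test or an alpha of its own.
- **Inclusion and exclusion criteria.** Contacts are eligible at "ages 6 months to 70 years".
- **Follow-up.** The 16 ml venous sample for anti-PGL-1, anti-LID-1 and IFN-γ is taken from adults and from those aged 12 to 17, at baseline, month 2 and month 12. "Children under 12 years of age will have only a digital pulp blood sample collected for rapid anti-PGL-1 test". The rapid test is done at baseline and month 12, and the section states that ELISA PGL-1 will be lacking in children.
- **Outcomes.** The PGL-1 and LID-1 secondary outcomes are serological status before and after chemoprophylaxis and before BCG, which places the second measurement at month 2.
- **Analyses of outcomes based on immunological and molecular parameters.** The marker variables are ELISA results, with optical-density cut-offs for PGL-1 and LID-1 positivity. "The response variables will include the anti-LID-1, anti-PGL-1, and IFN-γ measurements on a continuous scale". Logistic regression is named for PCR only.

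**The concern.** The power statements and the sampling plan use different denominators. If the 85/77/80% count every contact, they include children from whom the protocol takes no material for LID-1, IFN-γ or ELISA PGL-1. Each enrolled child under 12 then lowers the marker sample below the one used for the stated power.

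The effect of rifampicin on these markers is a declared study aim, and the Discussion presents the marker work as an advantage over the national pilot project. A marker comparison with no significant difference would probably be read against the published power, so that figure should refer to the people who can be measured.

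A second, smaller question is which comparison the figures describe. They are for differences in proportions, while the planned marker models use continuous values.

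**Working it through.** **Inputs from the protocol**

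- Control rates and differences: PGL-1 30% and 8 points; LID-1 2.5% and 2 points; IFN-γ susceptibility 35% and 8 points.
- Group sizes: 829 + 415 = 1244 evaluable; 995 + 498 = 1493 enrolled.
- Alpha: 5% for all analyses. The sample size section also mentions a correction to 0.025 for the interim analysis.
- Loss: 20% during follow-up.

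**Assumptions**

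- The difference is a decrease under rifampicin: 22%, 0.5% and 27% in the treated group.
- The share under 12 is not stated, so 10% to 30% is shown.

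**Method.** Power of the two-sided Fisher exact test (twice the smaller one-sided p-value):

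power = Σ over x, y of Bin(x; n_c, p_c) · Bin(y; n_t, p_t) · 1[p-value(x, y) ≤ α].

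**Step 1: reproduce the stated figures**

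| Control / treated | Two-sided α | PGL-1 | LID-1 | IFN-γ |
|---|---|---|---|---|
| Stated | – | 85% | 77% | 80% |
| 415 / 829 | 0.05 | 84.6% | 77.1% | 80.6% |
| 498 / 995 | 0.025 | 85.0% | 77.0% | 80.6% |

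Both rows fit, so the document does not identify the base. Neither row removes children. LID-1 is sensitive to the method: at 415/829 and two-sided 0.05, a z test gives 70.0% with unpooled variance and 81.9% with pooled variance. Fisher is used below because it matches all three figures.

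**Step 2: remove contacts under 12.** With a share f under 12, each group size is multiplied by (1 − f). For f = 0.10, 415 × 0.90 ≈ 374 and 829 × 0.90 ≈ 746. On the 1244 base at two-sided 0.05:

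| Share under 12 (assumed) | Control / treated | PGL-1 | LID-1 | IFN-γ |
|---|---|---|---|---|
| 5% | 394 / 788 | 82.7% | 74.7% | 78.5% |
| 10% | 374 / 746 | 80.5% | 72.4% | 76.2% |
| 20% | 332 / 663 | 75.5% | 66.7% | 71.0% |
| 30% | 290 / 580 | 69.6% | 60.0% | 64.7% |

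On the 1493 base at two-sided 0.025 the pattern is the same: 80.5/72.0/75.7% at 10% and 68.5/58.1/63.3% at 30%.

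The PGL-1 column applies to ELISA values at any visit and to every month-2 PGL-1 result. It does not apply to a month-12 comparison that uses the children's rapid test.

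**Step 3: allow for smaller loss at month 2.** The 20% covers the whole follow-up, and month-2 loss is not stated. Starting from 1493 at two-sided 0.05, with both percentages assumed:

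| Month-2 loss | Under 12 | Sampled | PGL-1 | LID-1 | IFN-γ |
|---|---|---|---|---|---|
| 5% | 10% | 1493 × 0.95 × 0.90 ≈ 1277 | 85.5% | 78.3% | 81.6% |
| 10% | 10% | 1493 × 0.90 × 0.90 ≈ 1209 | 83.5% | 75.7% | 79.4% |
| 10% | 20% | 1493 × 0.90 × 0.80 ≈ 1075 | 78.8% | 70.2% | 74.3% |

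With no loss at all, the share under 12 that still leaves 1244 is 1 − 1244/1493 = 16.7%. With the full 20% loss, 1493 × 0.80 ≈ 1194 remain before any child is removed, giving 83.1/75.2/78.9%.

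**The case against.** The strongest reply is that a shortfall is not demonstrated. The protocol gives neither the age mix nor the loss at month 2. With few children and little early loss, the enrolled 1493 leave enough samples at two-sided 0.05 to meet the stated power, as the first row of step 3 shows. This stands. A reader might infer that the design cannot deliver 85/77/80%, and the document does not support that at month 2.

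A reader might also take 1244 as the base that was used. The wording follows the 1493 total, and 1493 at 0.025 fits equally well. This stands too, but both bases count everyone.

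For PGL-1, the protocol says seropositivity without naming ELISA, and children have a rapid-test result at baseline and month 12, with a planned agreement check against ELISA in adults. So the PGL-1 part is limited to month 2 and to ELISA values.

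Finally, a reader might infer that the continuous analysis makes the true power lower than stated. It does not follow: a continuous model does not by itself lose power and may gain it. The outcomes are worded as serological status, cut-offs are given, and the list of continuous responses is not exclusive. What remains is that the text does not say which comparison the figures describe.

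These are secondary outcomes and do not determine the trial's size. That limits the weight of the point but does not make the denominator right.

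**Conclusion.** The point holds in this form: the stated marker power is recovered only by counting all contacts, and the sampling plan excludes those under 12 from LID-1, IFN-γ, ELISA PGL-1 and every month-2 marker. The figures as written therefore rest on a denominator that the design supplies only if no contact is under 12, or if unused loss allowance happens to offset the children.

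The size depends on two numbers that the protocol does not give. On 1244 evaluable contacts at two-sided 0.05, the loss of power is about 2 points with 5% under 12. With 30% under 12 it is about 15 points for PGL-1 (84.6% to 69.6%), 17 for LID-1 (77.1% to 60.0%) and 16 for IFN-γ (80.6% to 64.7%). At month 2 with low early loss and few children there may be no shortfall. All figures assume a decrease under rifampicin and a Fisher exact test.

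The primary outcome and its sample size are not affected.

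**What to change.** Restate power for LID-1, IFN-γ and month-2 PGL-1 using the expected number of contacts aged 12 or over with evaluable samples. Take the age mix from the trial's own recruitment so far, and use the expected loss at the visit concerned. For each figure give the visit, the alpha, the direction of the difference and the test. If month-12 PGL-1 is meant to include the children's rapid-test results, say so and give that figure separately.

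Say also whether the figures describe a comparison of proportions positive, which should then be named among the planned marker analyses, or replace them with power for the continuous comparison.

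The cost is one recalculated paragraph. No extra enrolment and no change to sampling are needed. The downside is that the stated marker power may become less favourable.

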## Discussion

The proposed study seeks to generate clinical and laboratory evidence that chemoprophylaxis combined with immunoprophylaxis may alter the natural course of subclinical infection by *M. leprae* by reducing the incidence of new cases and altering the laboratory parameters of infection. It is hoped that the results of the present study broaden the theoretical basis of the leprosy control program in Brazil.

The MH started a pilot project, referred to as PEP-hans, in a number of defined areas in the states of Pernambuco, Mato Grosso, and Tocantins in June 2015 [24]. The objective was to evaluate as closely as possible the effectiveness of postexposure chemoprophylaxis with one dose of rifampicin. The intervention is expected to reduce the risk of leprosy among contacts who present themselves to any health care facility nationwide under the Unified Health System (UHS), while keeping in mind the operational aspects involved in that initiative. Although PEP-hans evaluates the effectiveness of single-dose rifampicin in a population similar to the one in the present study, it differs in several methodological aspects such as the administration of rifampicin to contacts of index cases diagnosed up to 12 months beforehand and who received the BCG vaccine at baseline.

The authors consider that one of the advantages of the present study over PEP-hans is the evaluation of the immunological parameters before and after the administration of rifampicin (again, prior to the BCG vaccine) in the presence or absence of *M. leprae*. This strategy may expand our knowledge of the immune mechanisms that identify the contacts most susceptible to illness and may also contribute to the future development of diagnostic kits.

The ongoing MALTALEP clinical trial developed by Richardus et al. [25] also aims to evaluate the combined effect of single-dose rifampicin chemoprophylaxis and BCG immunoprophylaxis in new leprosy contacts. The present study shares the hypothesis that there is a combined effect of chemoprophylaxis and immunoprophylaxis but objectifies the gathering of information on the immunological parameters that have been influenced by the separate interventions in the same individual.

The above study and ours will carry out immunological and genetic analyses but at different times. MALTALEP will collect blood from 150 contacts in each randomized group within an 8-week period and within 1 and 2 years of follow-up. In our trial, however, blood collection will take place upon recruitment and then 2 and 12 months later. The results of these studies may be complementary to each other and, if so, be able to identify more effective strategies to manage contacts at greater risk and elaborate secondary preventive measures with rifampicin.

Research settings, particularly for experiments, may distance themselves from the “real world”, so that results may not be reproducible under typical operational conditions prevailing in average public health care units. In this regard, the proposed intervention is simple enough to be easily incorporated into routine practice. Conversely, the laboratory tests may pose additional difficulties for the public health care services. The present study addresses day-to-day medical issues, but the limitations of the external validity of the results should be acknowledged.

Leprosy is a millennial disease and, although it shows a low mortality rate in recent times, it continues to present high morbidity with the loss of the capacity to work accompanied by pernicious social stigmatization, often making it difficult to approach possible leprosy patient contacts.

Chemoprophylaxis represents an opportunity to increase the impact on contact control to prevent the rise of new cases while infection markers will allow the contacts with the highest potential to benefit from this intervention. The results of this trial could make a considerable contribution to the prevention and containment of leprosy and to a more robust clinical management of contacts who become infected**.** With the additional resources available for clinical investigation and prophylaxis, it may be possible to more readily engage leprosy contacts to fully comply with all medical recommendations.

